**Fig. 1 Fig1:**
[figure not shown]
Proposed experimental design and outcome measures at each testing time-point

An *a priori* power calculation using R statistical software and “WebPower” package (wp.kanova function) [57] was performed. Using an effect size based the median Cohen’s d extracted from several relevant studies investigating the effects of NHE on the primary aim of fascicle length changes [19, 21, 26, 54, 58] and converting to Cohen’s f (f = 0.8), 2 experimental groups (RDL vs. NHE), a total of 12 factors (levels of intervention x time x imaging location (proximal, mid-belly, distal) = 2 × 2 × 3), α = 0.05, and power = 0.80, a total sample size of 11 participants per group will be required. This sample size is consistent with previous investigations of fascicle length following NHE training [19, 21, 26, 54, 58]. Using a conservative effect size (Cohen’s d = 0.5) based on observed 2% differences detected in sprint times between two eccentric training interventions (Cohen’s d = 0.87) [47] and converting to Cohen’s f (f = 0.25), a total sample size of 28 (N = 14 per group) will be required for the secondary aims. Based on the larger sample size and accounting for a 10% attrition rate, a total of 16 participants per group (N = 32 in total) will be recruited from the University of Wisconsin to participate. Participants will be compensated on a pro-rated basis for completing study visits and provided their strength and sprint results.

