### Maximum sprint testing data collection

A minimum of 15 min between strength testing and sprints will be administered. Sprints will be performed on artificial turf to minimize any effects of weather and variations in ground surface conditions on sprint performance outcomes. Prior to sprinting, participants will be weighed for subsequent sprint kinetics analysis (see *Outcome Measures & Statistical Analysis*) and to determine an accurate mass for proper calibration of the IMU system.

Participants will go through a standardized warm-up (Additional File, Table A2) [2, 77]. Following the warm-up, the participants will rest for 5 min to allow for placement of eight IMUs (Xsens MVN, Xsens Technologies B.V., The Netherlands) on the sternum, sacrum, and bilaterally on the thighs, legs, and foot. This system is reliable and validated to measure joint kinematics during dynamic trials and related to sprint mechanics [78–80]. Once the system is successfully calibrated, participants will then perform three maximal 60 m sprints.

Timing gates (SmartSpeed, Vald Performance, Queensland, Australia) will be placed at the start line (0 m), 5, 10, 20, 30, 40, 50, and 60 m. Each participant will perform a total of 3 maximal 60 m sprints from a standing position with 90 s rest in between each trial to minimize the effects of fatigue. Participants will begin with their front foot 0.5 m behind the first timing gate to prevent premature activation of the timing gates.

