### Outcome measures & statistical analysis

All outcome results will be included in an anonymous database for statistical analysis. Using an intention-to-treat analysis, separate linear mixed effects models will be used to compare the effect of RDL and NHE on the primary outcome of biceps femoris long head fascicle length. Similar analyses will be performed for secondary analyses related to pennation angle, anatomical cross-sectional area, muscle thickness, and SWS. Full factorial models will be implemented with fixed effects of intervention group, muscle region, and time and a random effect to account for between-participant variation. Effect sizes will be calculated.

Sprint performance outcomes will be summarized using descriptive statistics. Given that the expected changes in sprint performance are numerically small but may still represent meaningful changes in overall sport performance and improvement, we will set *a priori* thresholds to describe the magnitude of change. Small, medium and large improvements in sprint times will be defined as < 2%, 2–4%, and > 4%, respectively, based off changes in 40 m sprint times observed previously [47, 82].

Discrete kinematic variables will be summarized using descriptive statistics and compared between time points for the maximal sprint using linear mixed effects models [83]. Due to the continuous time series data extracted from the IMUs, statistical parametric mapping (SPM) will also be used to determine any within-participant changes in kinematics throughout the entire sprint. SPM allows for the analysis of the entire time series and has been used in a variety of biomechanical studies [84–86]. Specifically, within-subject differences in trunk, hip, knee, and ankle kinematics will be calculated between test sessions

As an additional description of sprint performance, we will characterize the horizontal force production as detailed by Samozino et al. and adapted by others [1, 47, 87]. Descriptions of the theoretical maximal horizontal force (F_0_), velocity (v_0_), and maximal power output (P_max_) will be derived from participants’ split times and each participant’s body mass according to previous works [44, 88]. Intervention assessments for each variable across each time point will be compared using linear mixed effects models and R software [89, 90]

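### The small-improvement class for sprint times has no lower bound, and unchanged or slower times have no class, so any measured gain above zero is labelled an improvement

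*Protocol article*

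**What the plan says.** The rule is in the section Outcome measures & statistical analysis. Sprint times are handled descriptively: "Sprint performance outcomes will be summarized using descriptive statistics". The reason given for adding thresholds is that "expected changes in sprint performance are numerically small but may still represent meaningful changes in overall sport performance and improvement". The thresholds are set in advance and are "thresholds to describe the magnitude of change". The classes are: "Small, medium and large improvements in sprint times will be defined as < 2%, 2–4%, and > 4%, respectively". Their source is given as "based off changes in 40 m sprint times observed previously".

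The section gives no lower limit for the small class. It has no trivial or no-change class, no class for slower times, and no measurement error for the timing. It does not say whether the labels go to participants, arm means or between-group differences.

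Two other places bear on the point. Maximum sprint testing data collection describes three maximal 60 m sprints per session, 90 s apart, with gates at the start line and along the track ("0 m), 5, 10, 20, 30, 40, 50, and 60 m"), so a 40 m split is recorded. The sample-size paragraph under Overall study design starts the secondary-aim calculation from a sprint effect, "based on observed 2% differences detected in sprint times between two eccentric training interventions (Cohen’s d = 0.87"), and then plans on d = 0.5.

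**The concern.** A magnitude scale needs a region where the reader is told that nothing can be distinguished from no change. This one has none: its lowest rung begins immediately above zero, and its only vocabulary is improvement. A gain well inside timing noise gets the same label as a gain of 1.9%.

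Three features make this more than a matter of style.

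- The thresholds are the only interpretive rule that the section attaches explicitly to sprint times, so the labels are likely to carry much of the sprint-time message.
- Both arms train and there is no untrained control. An improvement label on a within-arm change cannot be separated from retest effects or noise.
- A sprint-time effect drove the larger of the two sample-size figures, so readers will look for a sprint result.

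What is at stake is a descriptive statement that both exercises gave small improvements in sprint time, made when the data are compatible with no change.

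**Working it through.** **Inputs from the protocol article.** Classes: small < 2%, medium 2–4%, large > 4%. Sprint effect: a 2% difference corresponds to d = 0.87; planned d = 0.5 (f = 0.25). Secondary-aim N = 28 (14 per group), raised to 32 for 10% attrition.

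**Input that is assumed.** The article gives no typical error (TE) for sprint times. I take 0.5%, 1.0%, 1.5% and 2.0% per session as a range.

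**1. The plan's own figures.** A repeated-measures group-by-time F test with f = 0.25, two groups, three time points, alpha 0.05 and an assumed within-person correlation of 0.5 gives N = 28 (power 0.812). Then 28 / 0.90 = 31.1, which rounds up to 16 per group, 32 in total. The figures reproduce under those settings. They do not depend on the labelling rule.

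**2. Where the planned effect falls.** Implied SD = 2% / 0.87 = 2.30 percentage points. Planned effect = 0.5 × 2.30 = 1.15%. This lies between 0 and 2%, in the same class as a change of nearly zero. The conversion assumes that the SD behind d = 0.87 is the relevant one.

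**3. Labels given to participants when the true change is zero.** The measured change between two sessions is taken as normal with mean 0 and SD = TE × √2. Then P(small) = P(0 < change < 2%) and P(medium or large) = P(change > 2%), with gains counted as positive.

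| Assumed TE | SD of change | Small | Medium or large | Any improvement label |
|---|---|---|---|---|
| 0.5% | 0.71% | 49.8% | 0.2% | 50% |
| 1.0% | 1.41% | 42.1% | 7.9% | 50% |
| 1.5% | 2.12% | 32.7% | 17.3% | 50% |
| 2.0% | 2.83% | 26.0% | 24.0% | 50% |

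The last column does not depend on TE. It follows from symmetry and a class boundary at zero. The split between the middle columns does depend on the assumed TE.

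**4. Labels given to an arm mean when the true change is zero.** With 14 per arm and TE 1.5%, the SD of the mean change is 1.5 × √2 / √14 = 0.57%. P(mean > 2%) = P(z > 3.53), about 0.02%, so a chance label of medium or large is negligible. P(mean > 0) is still one half, so the small label would be earned by chance about half the time.

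**The case against.** The strongest reply is that the rule grades improvements. A reader might infer that, because the lowest class is simply below 2%, a time that is unchanged or slower also counts as a small improvement. The text does not support that: a slower time is not an improvement, nor is zero change. Such results are left without a class. Percentages that count them as small need a signed reading of the threshold that drops the noun it qualifies, and I do not rely on them.

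Second, the labels are descriptive and attached to a secondary outcome. No test or success criterion depends on them, and they do not guarantee that an improvement is reported, since a slower arm mean would show in the descriptive statistics. That stands and limits the weight of the point.

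Third, half of results fall on the improved side for any noisy measure with no true change. That is true, but it is this rule that turns every one of those results into a named improvement.

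Fourth, the chance rates for medium or large labels rest on typical errors that the article does not give and on labelling individuals. That also stands; for an arm mean they almost vanish.

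Fifth, one might infer that 40 m cut-points are wrongly applied to a 60 m test. The article does not restrict the thresholds to the 60 m time, and a 40 m split is recorded. What is missing is only the name of the split.

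Sixth, a condensed article may leave detail to an analysis plan. Here, however, it states the rule in full with its cut-points, and nothing elsewhere in it supplies a floor.

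**Conclusion.** The point holds as a defect in a stated rule, of limited consequence. The small class begins at zero with no allowance for measurement error, and unchanged or slower results have no class. With no true change and symmetric error, about half of participants, or an arm mean about half the time, would be labelled improved. That result needs no assumption about the size of the error. The planned effect of about 1.15% falls in the same class as near-zero change, so the small label cannot tell them apart. Chance rates for the higher classes are illustrations under assumed typical errors. The primary analysis of fascicle length is not touched. The thresholds are meant to be set in advance, so the repair should be made before sprint results are seen.

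**What to change.** Amend the threshold rule in four respects.

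1. Add a trivial or unclear band around zero, with a floor at least as large as the typical error from the three baseline sprints already planned. Treat this as a minimum: sprints 90 s apart give within-session error, while the changes to be labelled span separate sessions.
2. Mirror the classes for slowing, so that every result has a class.
3. State that the 2% and 4% cut-points apply to the 40 m split, which is already timed, or justify them for 60 m.
4. Report the between-group difference in sprint-time change with its 95% CI, and apply the labels to that estimate, naming the arm it favours. The interval, not the label, should carry the interpretation.

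No new data are needed. The cost is revised wording, a typical-error calculation and one further estimate with its interval. The downside is that fewer changes will be called improvements.

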## Discussion

Although much research has been dedicated to identifying the etiology and mechanisms of injury, potential risk factors, residual neuromuscular deficits, and evidence-based recommendations for rehabilitation protocols of HSI [4, 6, 10, 13, 18, 91–102], the incidence and injury burden of HSI have not improved [14, 103]. The NHE is a staple in injury prevention programs for HSI, but evidence suggests adherence is a major limitation in its effectiveness for reducing HSI [104–107]. Due to the high rate of injury within the proximal muscle-tendon junction of the biceps femoris and non-uniform muscular adaptation to resistance training, different exercises should be employed to target specific muscle regions and increase eccentric training adherence [52, 53, 108, 109]

Consistent eccentric hamstring strength training (specifically using the NHE) increases eccentric knee flexor strength and influences architectural adaptations thought to be protective of HSI—such as increased fascicle length with concurrent decreases in pennation angle [47, 50, 54, 59, 60, 97, 110]. Fascicle length, pennation angle, and muscle thickness are typically measured using ultrasonography at the mid-belly [2, 47, 54, 59, 60], but this does not account for the known variation in architecture along the length of the hamstrings muscles [48, 49, 111, 112] or the non-uniform lengthening, activation, and adaptations induced by resistance training [113–116]. Recent evidence indicated that changes in fascicle and sarcomere lengths only occur in the distal region of the biceps femoris muscle following NHE training [50]. This coincides with higher neuromuscular activation in the distal region compared to the proximal and middle regions of the biceps femoris muscle during the NHE [117]. Our proposed investigation aims to determine if hip-dominant (RDL) or knee-dominant (NHE) eccentric hamstring exercises influence regional differences in fascicle length adaptations

Although ultrasonography is typically used to characterize architectural adaptations following eccentric exercise training, some ultrasound systems have capabilities that can provide insight into characterizing tissue material properties. Shear wave imaging has been shown to be a reliable, non-invasive, quantitative technique to characterize tissue stiffness in both tendon [118–120] and muscle [74, 121, 122]. Ultrasound elastography-derived shear modulus (derived from the SWS) has also been related to both passive and active muscular force production [123] as well as isometric rate of torque development in the gastrocnemius muscle [124]. Therefore, SWS may relate to both sprint performance and injury resiliency, but chronic adaptations following eccentric training have not been consistently established [23]. As an exploratory aim, we will measure regional SWS in the biceps femoris muscle to determine any chronic adaptations in tissue material properties following eccentric strength training

Resistance training, specifically eccentric training, has shown positive effects for both injury prevention and athletic performance. Despite extensive research showing the benefits of the NHE on reducing HSI risk [125], there is ongoing debate whether alternative exercises, such as the RDL, may offer similar or potentially even greater benefits. This is particularly debated with respect to the biceps femoris muscle, which is most frequently injured and appears to be more proportionally targeted in hip extension versus knee flexion exercises [17, 25, 26, 29, 52, 53]. While it is acknowledged that interventions aimed at hamstring injury prevention and improving sprint performance should be multi-faceted, comparing two commonly prescribed exercises like the NHE and RDL allows practitioners to prescribe hamstring exercises in an evidence-based manner with descriptions of the underlying muscular adaptations and implications for sprint performance improvements. The methods and proposed sprint analyses will allow for a comprehensive view of the effects of both the NHE and RDL on sprint mechanics through force-velocity profiling and kinematic changes throughout key phases of the sprint

The findings from this proposed study have practical applications for strength and conditioning coaches, athletic trainers, and physical therapists to address HSI risk factors and sprint performance through targeted exercise selections. In addition to providing information for evidence-based hamstring exercise selection, it is hoped that the findings of this study also inform future research projects aimed at investigating alternatives to the NHE, such as the RDL, in terms of their effectiveness in reducing rates of HSI in larger scale prospective intervention studies

## Data Availability

The anonymized dataset used for analysis will be made available from the corresponding author upon reasonable request.
